### Screening and randomisation

In the 24 h prior to hospital discharge, patients will be screened for eligibility and recruited. The recruitment strategy will involve a two-stream approach over an approximately 6-month period. In the first stream, potential participants will be identified by the stroke team. The second stream will involve pre-screening for potential participants using PowerTrials. Following potential participant identification, a member of the stroke team or a research assistant will approach all eligible people with minor stroke admitted to the recruiting hospital, thus allowing a fair recruitment strategy. Participants will be randomly allocated to receive usual care or the new service pathway. Randomisation will occur using a computerised random number generator (by the primary researcher) with 50:50 assignment to the new pathway or usual care (*N* = 55 participants per group). Assignment will be concealed using opaque envelopes. The participants and their families and the research assistant conducting the assessment sessions will be blinded to the intervention assignment. No circumstances are foreseen which will necessitate unblinding; however, if unblinding is required, the unblinding process for an individual participant will be conducted by the primary researcher.

Participants will consent to participate in the project using a written Participant Information and Consent Form (PICF). PICFs will be provided to potential participants by a member of the stroke team or research assistant. Potential participants will be informed that participation in the trial is entirely voluntary and that they can opt out of the trial.

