### Participants

One hundred ten participants diagnosed with minor stroke will be recruited while admitted as an inpatient following a minor stroke (See Fig. 1).

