### Sample size estimates

For a medium effect size (0.5) with 80% power for the 2 groups, 51 participants are required per group (calculated with G Power*2), increased to 55 to allow for dropout. Our previous project revealed that there were 2979 stroke admissions to the target hospital (Jan 2011-Jan 2017). Approximately 22% of stroke admissions met our inclusion criteria and were referred to our project, with 70% of eligible patients consenting to participate and being retained at follow-up.

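### The article's own admission and consent figures support about 41 recruits in the stated 6 months, not 110; at those rates 110 takes about 16–17 months

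*Protocol article*

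**What the plan says.** The Participants section sets the target: "One hundred ten participants diagnosed with minor stroke will be recruited while admitted as an inpatient following a minor stroke". Screening and randomisation repeats it as 55 per group, with "50:50 assignment to the new pathway or usual care", and gives the timetable: "The recruitment strategy will involve a two-stream approach over an approximately 6-month period". The two streams are identification by the stroke team and pre-screening with PowerTrials. Study setting and the eligibility criteria describe a single recruiting hospital.

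Sample size estimates derives 51 per group, raised to 55 for dropout, and then gives throughput figures from the team's previous project at the same hospital: "there were 2979 stroke admissions to the target hospital (Jan 2011-Jan 2017", then "Approximately 22% of stroke admissions met our inclusion criteria and were referred to our project", and finally "70% of eligible patients consenting to participate and being retained at follow-up".

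The article mentions no further site and gives no figure for a rise in admissions or for a higher expected yield in this trial.

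**The concern.** The throughput figures stand in the sample size section, where their evident purpose is to show that 110 is attainable. Combined with the recruitment period in the next section, they show the opposite: the historical flow through this hospital supplies well under half of the target in 6 months.

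The recruitment period is a planning figure that others rely on. The weekly facilitated education sessions and the blinded assessments have to be staffed for as long as recruitment and follow-up last, and 6 months understates that by a factor of two to three. If the period were also a fixed limit set by funding or staffing, the comparison on the primary outcome would be made with far fewer participants than the power calculation assumes.

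**Working it through.** **Inputs**

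- Sample size estimates: 2979 admissions, January 2011 to January 2017, taken as 72 months (73 as a sensitivity check); 22% eligible and referred; 70% of eligible patients consenting and retained; effect size 0.5; 80% power; 51 per group raised to 55.
- Participants, and Screening and randomisation: 110 in total, 55 per group, about 6 months.
- Assumption: alpha and sidedness are not stated, so power is shown both ways at alpha 0.05.

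**The plan's own figures**

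A two-sample t-test with d = 0.5, 80% power and one-sided alpha 0.05 needs 50.2, so 51 per group, which reproduces the plan. A two-sided test needs 63.8, so 64, which does not. The step from 51 to 55 implies a dropout allowance of 1 − 51/55 = 7.3%. The article shows no derivation for the 6-month period.

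**Flow in 6 months**

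- Admissions: 2979/72 = 41.4 per month; × 6 = 248.
- Eligible and referred: 248.25 × 0.22 = 54.6.
- Consenting and retained: 54.6 × 0.70 = 38.2.

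The 70% combines consent with retention, whereas 110 is a number recruited that already allows for dropout. To compare like with like, divide out the plan's own retention:

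- Implied consent: 0.70/(51/55) = 75.5%.
- Recruited: 54.6 × 0.755 = 41.2, against 110.
- Equivalently, 38.2 retained against 2 × 51 = 102.

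**Months needed for 110**

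| Share of eligible, referred patients recruited | Recruits per month | Months to 110 |
|---|---|---|
| 75.5% (retention separated out) | 41.2/6 = 6.87 | 16.0 |
| 70% (whole figure read as the recruitment rate) | 38.2/6 = 6.37 | 17.3 |
| 100% (nobody declines) | 54.6/6 = 9.10 | 12.1 |

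With 73 months the three results are 16.2, 17.5 and 12.3.

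**What 6 months would require**

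- 110/248.25 = 44% of all stroke admissions would have to be recruited.
- Even with full consent, the eligible-and-referred share would have to double from 22% to 44% (110/54.6 = 2.01). At a 70% yield it would have to be 110/0.70/248.25 = 63%.
- Chance variation does not bridge the gap. With 54.6 expected, the Poisson probability of 110 or more is about 3 × 10⁻¹¹.

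**Power for d = 0.5, only if recruitment did stop at 6 months**

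| Per group | Basis | Two-sided 0.05 | One-sided 0.05 |
|---|---|---|---|
| 19 | 38.2/2 | 32% | 45% |
| 27 | 54.6/2 | 44% | 57% |
| 51 | plan | 71% | 81% |

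These are two-sample t-test figures, in line with the article's own calculation. The planned analysis is a mixed model for repeated measures, so they are approximate.

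**The case against.** Four points can be made for the plan.

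1. *The 22% may understate eligibility.* It counts patients who both met the criteria and were referred in an earlier project. This trial adds a PowerTrials stream and intends to approach every eligible patient, which could recover missed referrals. The admissions figure is also a flat average ending in January 2017, the trial was registered in January 2019, and the Background describes growing numbers of minor strokes. This stands in part: 55 is an estimate at historical rates, not a hard ceiling. But the article quantifies none of these gains, and the yield would have to double even if nobody declined.

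2. *The 70% includes retention.* This is correct. Setting 38 directly against 110 would count attrition twice. The comparable number recruited is about 41, which moves the time needed from 17.3 to 16.0 months and leaves the conclusion unchanged.

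3. *The sample size governs and the 6 months is only a forecast.* This also stands. The article fixes 110 in several places, calls the period approximate and gives no closing date. A reader might infer that the trial will end with about 38 participants and be unable to answer its primary question. The document does not support that, because it contains no calendar stopping rule.

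4. *A journal article leaves logistics to the full protocol.* That would answer a complaint about an omission. Here, two stated sets of figures in adjacent sections disagree.

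**Conclusion.** The concern holds as an inconsistency between the recruitment period and the feasibility figures. At the historical rates, 6 months at one hospital yields about 55 eligible and referred patients, about 41 recruited and about 38 retained. Recruiting 110 takes about 16–17 months, or about 12 with full consent. The word approximately cannot stretch 6 months that far.

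The result rests on three assumptions: that the 2011–2017 admission rate still applies, that the 22% and 70% carry over from the earlier project, and that dropout matches the plan's 51-to-55 allowance.

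Two stronger readings should be resisted. The first is that 6 months and 110 are strictly incompatible; the historical figures fail to support the pairing, but a justified doubling of yield would reconcile it if nobody declined. The second is that the trial will be underpowered because of its timetable; that follows only if 6 months is a fixed limit. Quoting 32% power alone would also overstate the loss, since the plan's 51 per group reproduces with a one-sided test, under which the figure at 19 per group is 45%.

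The design, outcome, analysis and required number are untouched. It is a wrong planning figure that should be fixed, not a defect that must be cured before the trial can proceed.

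**What to change.** In Screening and randomisation, restate the recruitment period as about 16–17 months at the single hospital. Alternatively, keep a shorter period and state and justify the higher yield or the added sites behind it; 6 months at this hospital needs about twice the historical eligible-and-referred rate even with full consent. In either case, add a sentence that recruitment closes when 110 participants have been randomised.

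Only if 6 months is a fixed limit, restate the expected size as about 38–41, at most about 55 at historical rates, and give the power for d = 0.5: about 32% two-sided or 45% one-sided at 19 per group, and about 44% or 57% at 27 per group. The study should then be presented as one of feasibility and estimation.

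The cost is a longer calendar period for the existing staff and education sessions, and submission of the changed timetable to the ethics committee, which the article requires for any protocol change. The sample size does not increase.

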### Hypothesis

The new pathway will reduce unmet needs at 1 and 3 months and improve functional outcomes, QOL, return to work and service access of minor stroke patients compared to usual care.

Note. Usual care (Control condition): This group will receive the usual care provided to minor stroke patients discharged from the recruiting hospital. This includes provision of an electronic discharge summary to the patient’s General Practitioner (GP) from the hospital treating team and a hospital outpatient follow-up appointment. Requirement for outpatient follow-up is determined at the time of discharge depending on the patient’s medical issues. Additionally, a My Stroke Journey booklet, discharge planning pack, counselling about stroke, medications and follow-up, are often available for patients, although this is not specific to minor stroke. Patients may be referred to private allied health providers or community services at the discretion of the treating team.

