### Intervention

Intervention: New service pathway: A multi-component pathway comprising 3 parts:
Self-management kit: Immediately prior to hospital discharge patients will receive a written information pack from the research assistant (with verbal support at the time). Self-management programs are effective approaches in stroke management [21, 22] and are recommended in the Stroke Foundation Clinical Guidelines for Acute Stroke Management [3]. The kit will include written information about common difficulties specific to minor stroke, the need to see a General Practitioner (GP) after discharge from hospital for ongoing support, need for medications, referral to allied health services, and issues for the patient to discuss with their GP (via checklist). Participants will also receive the My Stroke Journey from the Stroke Foundation, which is a booklet available to all stroke patients in Australia about general stroke information.Customised screening checklist: To encourage patients to undertake self-management in collaboration with their GP, patients will be provided with a checklist to share with their GP. The checklist will include questions about services accessed and residual difficulties/changes post-stroke.Minor stroke sessional educational topics: Patients will be informed about a weekly program of minor stroke community-based educational topics delivered as a group program. These sessions will be facilitated by a qualified health professional and will be scheduled for 1.5 h weekly at rotating locations. Education sessions have been identified as a critical ingredient of successful self-management programs in chronic disease [23]. The group sessions will include brief information about common problems following minor stroke, return to work and driving, need for medications, issues to discuss with GPs, and will have a guest speaker from a different health discipline each time (e.g., physiotherapy, occupational therapy). Information will be “bite sized” (i.e., brief) [24] and patients will receive a short, written summary to take home. The final part of each session will be social, providing patients with a chance to discuss issues, build relationships and receive peer support. To improve adherence/attendance at the education sessions, participants will be sent a text reminder approximately 24 h before each session reminding them of the upcoming session.

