### Outcomes

All participants will complete an initial face-to-face assessment. This will be repeated 1- and 3-months post-discharge. The research assistant administering the assessments will be blinded to participant randomisation group.

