#### Primary outcome measure

Survey of Unmet Needs (SUNSU) [13]: Self-rating scale determining needs across impairment, activities of daily living, occupational activities, psychological needs, and community access. The SUNSU has 27-items (e.g., “Travelling in my community”). Participants tick beside an item if they are receiving help with that item and/or if they want help with that item. Each item is scored as “0” if participants do not receive/require help with that item, or “1” if participants require help with that item (therefore scores for each individual item range from “0” no help received or required for that item to “2” help received and required for that item). Higher scores represent more needs. The SUNSU has good person separation reliability and internal consistency scores [13].

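### The plan states that participants and families are blinded, which an open service pathway with a self-rated primary outcome does not allow, and it does not separate kit delivery from blinded assessment

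*Protocol article*

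**What the plan says.** Under Screening and randomisation the protocol article claims three layers of blinding in one sentence: "The participants and their families and the research assistant conducting the assessment sessions will be blinded to the intervention assignment". It adds that no need for unblinding is foreseen, and that the primary researcher would unblind an individual participant if it became necessary. Outcomes repeats the claim for the assessor: "The research assistant administering the assessments will be blinded to participant randomisation group". Statistical analysis adds that the analysis is done blind to group, and that the research assistant who runs each assessment session also enters and codes its data.

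Intervention describes what the pathway arm receives. On the kit: "Immediately prior to hospital discharge patients will receive a written information pack from the research assistant (with verbal support at the time". On the group programme: "Patients will be informed about a weekly program of minor stroke community-based educational topics delivered as a group program". On reminders: "participants will be sent a text reminder approximately 24 h before each session reminding them of the upcoming session". There is also a checklist for the patient to take to the general practitioner, and participants may take up all or only some of the components.

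For the control arm, the note under Hypothesis says: "This group will receive the usual care provided to minor stroke patients discharged from the recruiting hospital". No sham or attention control is described. The primary outcome, the SUNSU, is introduced as a "Self-rating scale determining needs across impairment, activities of daily living, occupational activities, psychological needs, and community access". Secondary outcome measures includes interviews with about 25 intervention-group patients on their perceptions of the programme.

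**The concern.** A blinding statement tells readers how far knowledge of the allocated arm could have influenced the results. Here it covers the people who supply the primary outcome. If participants know that they are in the arm with the new service, that knowledge can affect how they judge and report their own unmet needs. Blinding the person who administers the form, or the analyst, does not remove that route. A trial reported as participant-blinded on this wording would misstate its risk of bias on its main endpoint.

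The second issue is the assessor. If the person who hands over the kit also carries out the assessments, that person knows the allocation of every pathway participant who was given a kit. An assessor who has learned the allocation cannot be made blind again later. The text should exclude this, and it does not.

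**Working it through.** The claim contains no figure, so the check sets the sections side by side.

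**Participants and families**

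1. *What is claimed.* Screening and randomisation says that they are blind to the assignment itself. It does not limit the claim to the hypothesis or to some feature of the comparison.
2. *What the pathway arm sees.* Intervention lists a kit specific to minor stroke explained in person, a checklist to share with the general practitioner, weekly group sessions of 1.5 hours, and a text before each session. None of these is described for the control arm. The general stroke booklet, My Stroke Journey, is given to the pathway arm and is often available under usual care, so it does not distinguish the arms.
3. *What would hide the difference.* A sham kit or an attention-matched programme might. The note under Hypothesis describes neither.
4. *What else reveals the arm.* Participants can choose among the pathway components, and about 25 of them are interviewed about the programme. Both presuppose that they know they are receiving it.
5. *Result.* For the 55 participants planned for the pathway arm, blinding to assignment is contradicted by the description of the intervention. The individual unblinding procedure assumes a participant blind that this arm does not have.

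**Primary outcome**

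6. On the SUNSU, participants tick whether they receive or want help with each of 27 items, so the participant is the rater.
7. The EXITS, SF-36 and SSQOL are also answered by the participant.
8. *Result.* Even with a perfectly blinded research assistant and analyst, these outcomes are rated by people who are not blind in at least one arm.

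**Assessor**

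9. Screening and randomisation, Outcomes, and Statistical analysis all identify the blinded or data-entering person by the task of assessing. Intervention has the kit delivered by a research assistant, with no further description.
10. Screening and randomisation also has a research assistant, with the indefinite article, approaching patients. More than one may therefore be employed.
11. The timing brings the tasks together. Recruitment takes place in the 24 hours before discharge, the first assessment is before discharge (Abstract), and the kit is given just before discharge.
12. *Result.* No sentence says that the two roles are held by different people, and none says that they are held by the same person.

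**The case against.** The strongest defence concerns the assessor. A reader might infer that the assessor is unblinded from the day of discharge for every pathway patient. The documents do not support that. Wherever blinding is claimed, the article specifies the research assistant who does the assessing, which suggests that others exist. It never says that this person hands over the kit. An article also commonly leaves staffing detail to the full protocol. This stands, and it reduces the assessor part to a request for one clarifying sentence.

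A second defence is that participants could be kept unaware of the hypothesis, or of which package is the new one. Controls often receive a booklet, a discharge pack and counselling, so they may not readily work out their arm. The consent material that would show what participants are told is not available here. This stands in part. It makes a precise statement of what is concealed an acceptable alternative correction, but it does not rescue a claim of blinding to the assignment.

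A third point is that an open comparison is close to unavoidable for an education and self-management pathway, so rewording will not remove reporting bias. That is true. The fault lies in describing the trial as something it is not, and choosing an open design is no fault in itself.

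A reader might also want a number, for example a bias of 0.1 to 0.2 SD, which would be 0.1/0.5 = 20% to 0.2/0.5 = 40% of the planned effect of 0.5. Nothing in the documents anchors that range. The percentages only divide an assumption by the planned effect, so they are not part of the finding.

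**Conclusion.** The point holds in two parts of different strength.

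- **Participants and families: wrong as written.** The stated blinding to assignment conflicts with the article's own description of the pathway and comparator. Because the SUNSU is self-rated, the primary outcome cannot be reported as blinded. This should be corrected before the trial is conducted or reported under that description.
- **Assessor: unresolved.** The article does not say whether the research assistant who delivers the kit also assesses. If the roles are already separate, the blinding claim for the assessor can stand once this is stated.

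The first part rests on the absence of any sham or concealment in the text shown. The direction and size of any bias cannot be quantified from the documents. The correction changes neither the sample size nor the planned analysis.

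**What to change.** 1. Under Screening and randomisation, replace the claim for participants and families with a statement that they are not blinded. Alternatively, specify exactly what they are kept unaware of, such as the study hypothesis, and how. Limit the blinding claim to the outcome assessor and the analyst, and bring the sentence on individual unblinding into line.
2. Acknowledge that the SUNSU and the other self-reported outcomes are open to reporting bias because participants know what they are receiving.
3. Under Intervention, require that the kit and the information about the sessions be handed over by an existing team member who conducts no assessments, after the baseline assessment is complete. Use the same role names under Outcomes and Statistical analysis.

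The cost is a less favourable risk-of-bias statement, a few sentences of text, and some scheduling of one short task before discharge. The article gives no staff numbers, so the scheduling burden cannot be stated more exactly.
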